### TAU

The foundation of TAU is to maintain treatment with at least one FDA approved mood stabilizer and to follow the recommendations summarized in the evidence-based stages of Texas Implementation of Medication Algorithm (TIMA) revised guidelines [43]. For all patients, TAU will require the presence of at least one FDA-approved mood stabilizer and antidepressant medications will only be prescribed in combination with a mood stabilizing drug, as described in the TIMA guidelines.

### Medication management

All participants will receive usual treatments for bipolar disorder [90] provided by either the investigator, clinical psychiatrists or psychiatry residents trained, certified, and supervised in optimal treatment practices for bipolar disorder within investigator-directed clinics. Where medication checks are being provided by non-investigator clinicians, the role of the investigator will be to monitor and/or influence/advise treatment taking place in their clinic.

Medication checks will take place every 2–4 weeks during the Open Stabilization Phase and/or as clinically indicated and weekly during the 1-month Observation phase. Medication checks during the Relapse Prevention Phase will take place every 2 months as clinically indicated. The frequency of medication checks will be adjusted as clinically appropriate at any time during the study based on the current clinical status of subjects in the study.

The CGI-S-BP for Overall Bipolar Illness, for Depression, and for Mania will be completed by the treating psychiatrist at every medication check. For subjects who are believed to be relapsing, the treating psychiatrist will complete a DSM-IV mood episode checklist for major depressive episodes, manic episodes, and mixed episodes.

### Physical and laboratory monitoring

During the baseline period, vital signs and weight will be recorded. In addition, an EKG will be required for participants over the age of 40 as clinically indicated. The EKG requirement will be waived if an EKG had been obtained within 3 months of the baseline visit and a report is available. Laboratory assessments of BUN, creatinine, electrolytes, TSH and a urine pregnancy test (if applicable) will be obtained at baseline and will be repeated based on APA guidelines for recommended lithium monitoring (see Tables 1 and 2). Drug screens will not be routinely administered; however, administration of drug screening as part of ongoing treatment is at the discretion of the treating physician at any time, after consultation with the participant.

**Table 1 Tab1:** Lab monitoring schedule

	Baseline	Stabilization		O^a^	M^b^
Test	Baseline	2 weeks	12 weeks	16 weeks	Every 6 months during 24 months of additional follow-up
Vitals/Weight	X		X		X
EKG^c^	X if age > 40				
BUN	X		X		X
Creatinine	X		X		X
Pregnancy	X				
TSH	X		X		X
CBC	X				
Electrolytes	X		X		X
Lithium	X	X	X	X	X
Genetics Samples	X				

^a^Observation phase

^b^Maintenance phase

^c^If clinically indicated, as determined by the study physician

**Table 2 Tab2:** Assessment schedule (time in weeks)

	B	Stabilization						O	Maintenance
	-1	0	4	8	12	14	16	Q 2 wks × 8 wks then monthly visits	Cross over to Valproic Acid for mood episode on lithium
CGI-S-BP by doctor	X	X	X	X	X	X	X	X	X
Mood episode checklist	X	X	X	X	X	X	X	X	X
Consent	X								
MINI- PLUS	X								
Demographics/course of illness	X								
HAM-A		X			X		X		X
MADRS		X	X		X		X	X	X
QIDS-SR 16	X	X	X	X	X	X	X	X	X
YMRS/CARS – M		X	X		X			X	X
Side Effects Survey	X	X	X	X	X	X	X	X	X
Q-LES-Q	X				X		X		X
IRS	X				X		X		X
MSSI	X	X	X		X		X		X
Serious Adverse Event Form	X	X	X	X	X		X	X	X

*O* observation phase, *B* baseline, *ET* Early Termination, *Mini-PLUS* Extended Mini-International Neuropsychiatric Interview, *MADRS* Montgomery Asberg Depression Rating Scale, *QIDS-SR 16* Quick Inventory of Depressive Symptomatology Self-Report, *YMRS* Young Mania Rating Scale, *CARS-M*: Clinician Administered Rating Scale for Mania, *HAM-A* Hamilton Anxiety Rating Scale, *CGI-BP* Clinical Global Impressions of Severity - Bipolar Version, *Q-LES-Q* quality of life, enjoyment, and satisfaction questionnaire, *IRS* impulsivity rating scale, *MSSI* The Modified Scale of Suicidal Ideation

### Assessments

Demographics: Age, sex, years of education, race, marital status, income, smoking status, employment history, and other demographic information will be recorded at baseline. The course followed by these patients after the study ends may offer rewarding opportunities to assess genetic correlates of long-term outcome in a sample with well-documented treatment responses. For this reason, we will also ask subjects to provide consent for future contact, as well as the names, addresses and telephone numbers of two individuals likely to know the subject’s future whereabouts, and the subject’s driver’s license number.

### Diagnosis

The Diagnostic Interview for Genetic Studies (DIGS) will be used to make DSM-IV diagnoses and to collect detailed historical clinical information. This instrument was developed to obtain very fine grain information about the symptoms and course of bipolar disorder. It has also been modified to collect retrospective medication response information. It has been validated by numerous studies and used for our collection of 4,500 subjects.

### Clinical course

Data will be collected on course of illness prior to randomization, including age of onset for bipolar disorder, number of prior episodes, past treatment response, childhood abuse (emotional, physical, sexual), medical conditions, psychoactive substance use, family history, prior lithium treatment and prior suicide attempt history, including lethality. Specifically, a history of episodes in the previous 2 years will be taken using a life chart method. This will be used as a covariate to correct for natural course in the statistical analysis.

### Symptom severity

Clinical Global Impressions of Severity Scale-Bipolar Version (CGI-BP) [44]. The CGI-BP is a modified version of the original CGI designed specifically for use in assessing global illness severity and/or change in patients with bipolar disorder; it assesses overall bipolar illness, depression, and mania. While the original CGI has been criticized for lack of reliability, the CGI-BP has been shown to have excellent inter-rater reliability. Not surprisingly, placebo response rates have been shown to be lower with the CGI-BP, compared to the HAM-D or MADRS in bipolar disorder. In contrast to symptom-severity scales, the CGI-BP is an integrated measure of illness severity that permits the incorporation of an assessment of function at work, social, family settings, etc. In contrast to the MADRS and HAM-D, it is not encumbered by the inability to distinguish improved somatic function (appetite and sleep) from medication-induced adverse events, which is important when studying medications that cause weight gain or somnolence.Montgomery Asberg Depression Rating Scale (MADRS) [45]. A 10-item clinician-rated measure of depression will be used to examine the extent of each patient’s current depressive symptoms.Young Mania Rating Scale (YMRS) [46]. An 11-item, clinician-rated measure that queries symptoms of mania.Clinician Administered Rating Scale for Mania (CARS-M) [47]. The CARS-M is a reliable and valid 15-item, clinician-rated measure of mania The CARS-M incorporates a number of methodological improvements in comparison to more frequently utilized mania rating scales, such as the YMRS. For example, the CARS-M separately assesses the presence of psychotic symptoms (e.g., delusions and hallucinations). Given the overlap in symptoms assessed on the YMRS and CARS-M, an integrated version will be developed and utilized for the current study, minimizing patient burden, yet allowing full-scale scores to be derived for each measure.Quick Inventory of Depressive Symptomatology Self-Report (QIDS-SR16) [48]. A 16-item self-report measure of depressive symptoms.

### Neurocognitive assessment

Neurocognition will be assessed for several reasons. Bipolar subjects with cognitive deficits may comprise a distinct group with a different disease mechanism. If this is the case, neurocognitive measures may correlate with response and serve as an endophenotype for response [49], substantially increasing the power to detect genes. Another reason has to do with side effects. Not only are such deficits part of the core bipolar phenotype, they may also be induced by medications. Cognitive slowing is a not uncommon side effect for many mood stabilizers. Testing may enable us to determine if these are markers for response, side effects or relapse, and if they are associated with specific genes.

Based on a review of previous published data on cognitive dysfunction in bipolar disorder and the heritabilities of several neurocognitive measures, our overall assessment strategy will focus on a brief measurement of three domains: attention, verbal learning, and executive function. The proposed neurocognitive battery can be administered in approximately 25 min and will consist of 5 measures (see Spreen & Strauss, 1998 for test citations):Wide Range Achievement Test (3 minutes) - Third Edition, Reading (WRAT-3). The WRAT-3 Reading subtest assesses single-word reading skill.WAIS-III, Digit Symbol Subtest (3 minutes). The WAIS-III Digit Symbol subtest task measures both visual scanning and graphomotor speed.The Stroop Color Word Test (SCWT) (4 minutes) (Golden version). The SCWT is a commonly used executive functioning task measuring inhibitory or cognitive control.Controlled Oral Word Association Test (5 minutes). The COWAT measures the ability to verbally produce words and is considered by most neuropsychologists to be a task of executive function.California Verbal Learning Test (CVLT) (15 minutes). The CVLT measures the processes and strategies involved in learning and retaining verbal material. Recent data support a familial component for impaired performance on the CVLT in bipolar disease patients and their unaffected co-twins [50]. COMT genotype has been associated with performance on the CVLT in patients with bipolar I disorder [51].

### Quality of life and functioning

Quality of Life, Enjoyment, and Satisfaction Questionnaire (Q-LES-Q) [52]. Assesses subjective quality of life (i.e., physical health, subjective feelings, leisure activities and social relationships).

### Impulsivity and suicidal behavior

Impulsivity Rating Scale (IRS). [53] The IRS is a 7-item clinician-rated assessment of impulsivity. It uses a 0 to 3 scale to rate irritability, impatience, decision-making, distractibility, aggressiveness, response control, and delayed gratification.The Modified Scale for Suicidal Ideation (MSSI*).* [54] The MSSI is an 18-item clinician-administered scale that monitors intensity of ideation, courage and competence to attempt suicide, and talk and writing about death over the past year. The first 4 items have been designated as screening items to identify those individuals whose suicide ideation is severe enough to warrant the administration of the entire scale. Each item is rated on a 0-3 point scale, and the ratings are summed to yield a total score ranging from 0 to 54.

### Side effects

Frequency and Intensity of Side Effects Ratings. A 3-item self-rated measure of medication side effects.

### Serious adverse events (SAEs)

SAEs will be systematically recorded to assess any life-threatening events or hospitalizations. An SAE is defined as any adverse drug experience occurring at any dose that results in any of the following outcomes:life-threatening event, including suicide attemptsdeathhospitalization/prolongation of hospitalizationcongenital anomalypersistent or significant disability/incapacityrequired intervention to prevent permanent impairment/damage

### Definitions of lithium relapse and spectrum of efficacy

There is emerging consensus that compounds that possess relapse and recurrence prevention efficacy in bipolar disorder stabilize mood by different mechanisms. Compounds that stabilize mood from both above and below baseline are viewed as having bimodal efficacy, e.g., they are able to delay or prevent both depressive and manic episodes. Those that stabilize mood by delaying or preventing episodes from below baseline are described as having the ability to delay or prevent depressive episodes without causing treatment-emergent mania, whereas those that stabilize mood from above baseline are believed to delay or prevent manic episodes without causing treatment-emergent depression. To identify pharmacogenetic predictors of spectrum of efficacy by mood state, the following definitions of relapse will be used:Manic Relapse will be defined as patients who meet DSM-IV criteria for a manic episode but not a major depressive episode.Depressive Relapse will be defined as patients who meet DSM-IV criteria for a major depressive episode but not mania or hypomania. In addition, the duration of the episode must be 4 weeks instead of 2.Mixed Relapse will be defined as patients who meet the DSM-IV criteria for a major depressive episode and a manic episode.Clinician’s Judgment. In addition to the DSM-IV defined relapse criteria, a patient may be deemed a relapse if, in the judgment of the treating physician, the current regimen is not working and it is clinically necessary to make a change in medications.

### Criteria for discontinuation

Participants may be discontinued from the study at any time at investigator discretion. Specific reasons for discontinuing are 1) withdrawal of informed consent; 2) pregnancy; 3) clinically significant or serious adverse event not consistent with continuation in study, as determined by investigator or participant; and 4) suspension or termination of the study, study site, or at investigator discretion.

### Valproate crossover

Participants who are unable to tolerate lithium or fail to achieve relapse prevention on lithium will be crossed over to treatment with valproic acid in an identically designed second phase, including a 3-month stabilization phase, 1-month observation phase, and a relapse prevention phase of up to 24 months. Measurement of valproate response in a subset of subjects will make it possible to test whether SNPs associated with lithium response are also associated with valproate response.

### IPSC studies of lithium response

We propose to create cell-based human models for lithium response in bipolar disorder by reprogramming skin fibroblasts from lithium-responsive and non-responsive bipolar disorder patients into human induced pluripotent stem cells (hiPSCs) (Fig. 1). By differentiating these disorder-specific hiPSCs into neurons, we hope to not only identify specific neuronal defects associated with bipolar disorder neurons in vitro but also elucidate the molecular and cellular mechanisms of lithium responsiveness and non-responsiveness in bipolar disorder.

**Fig. 1 Fig1:**
[figure not shown]
iPSC-derived neurons as a cellular model of bipolar disorder and lithium response. Fibroblasts are grown from skin biopsies taken from participating subjects. These cells are treated with a combination of four transcription factors that reprogram the cells to stem cells. These iPSCs are then treated with a series of growth factors to differentiate them into a variety of neuronal types. In this way, neurons from patients can be compared to controls or lithium responders to non-responders

### Gene expression studies will be used to identify high-priority candidate genes and to study gene networks

In particular, gene expression will be studied using RNA-seq in cells from responders and non-responders treated with and without lithium, as illustrated in Fig. 2. Genes whose expression is significantly changed in response to lithium in responders but not non-responders will comprise a set of high-priority candidate genes for further study. This set of genes will then be used for detailed genotyping and sequencing studies of the DNAs from the prospective study participants. By using biology to develop a reduced set of a priori selected candidate genes, we can substantially reduce the number of statistical tests and preserve the statistical power of our sample. This strategy assumes that some of the same genes displaying differential change in expression also contain the variants affecting lithium response. Candidate genes may also be selected from other sources such as published literature or results from the ConLiGen consortium, animal or cellular studies.

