### Lithium-mediated gene expression

There are likely hundreds if not thousands of genes that are modulated in some way by lithium. Data have been emerging for the past several years that clearly demonstrate lithium-mediated gene expression changes. Bosetti et al. reported changes in the expression of a variety of genes in response to lithium, including those from signal transduction pathways [28]. The study of a larger gene array with 39,000 transcripts in mice [29] reported 4,474 genes with nominally significant expression changes and 121 with a stringent Bonferroni correction. There were 13 genes affiliated with phosphotidylinositol metabolism, again consistent with the cell signaling pathway hypothesis. One of the more comprehensive studies reported to date used a human neuronal cell line (SK-N-AS), and they reported 347 upregulated and 324 downregulated genes, from 3 primary pathways: the mitogen-activated protein kinase (MAPK) signaling pathway, an actin cytoskeleton pathway and a calcium signaling pathway [30].

Expression patterns of micro RNAs (miRNA) in the hippocampus of rats have shown that lithium and valproate both decreased the expression of several miRNAs considered candidates for bipolar disorder; including the pathways involving Wnt/βcatenin [31]. A study of miRNA in lymphoblastoid cell lines found increased expression when exposed to lithium, with a clear variation in expression patterns with time, reflecting the dynamic biological system wherein gene expression is unlikely to be static [32].

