#### Specific aims

A prospective trial of mood stabilizer response will be conducted at a group of 11 closely collaborating sites.The study will have an algorithmic design. All patients will be started on lithium. Those that fail lithium will be crossed over to valproic acid (VPA). Those that fail VPA will be crossed over to a standardized treatment as usual (TAU) arm.The study will be designed to identify genes for relapse prevention. All patients will be stabilized on lithium monotherapy and then enter the maintenance phase where they will be followed for 2 years or until relapse. On relapse, they will be discontinued or crossed over as appropriate.The prospective sample will be genotyped for GWAS. Positive SNPs from the Consortium on Lithium Genetics (ConLiGen) will first be selectively tested to control multiple comparisons. Following this, a complete GWAS on the prospective sample will be performed as well as a meta-analysis with ConLiGen.Mechanistic studies of lithium response will be conducted as part of the project.Skin biopsies will be collected on 100 patients from the prospective study. Fibroblasts from 10 lithium responders and 10 non-responders will be reprogrammed to induced pluripotent stem cells (iPSCs).iPSCs will be differentiated into neural progenitor cells (NPCs) and then into mature neurons.Pathways will be identified that are altered in lithium responsive vs. non-responsive NPCs and mature neurons. Cells will be treated with and without lithium and RNA-seq will be conducted. Genes whose expression is altered by lithium in lithium responders and not non-responders will be identified as possibly involved in lithium response. SNPs in these genes will be tested for association with response in the human prospective data. Similarly, genes associated with lithium response in the human studies will be tested for change in the cell culture models. Network and pathway analysis will be applied to the expression data. Expression in iPSC-derived neurons will be used to predict networks of related genes. These networks will be tested as groups of genes in the human association data.Specific neuronal deficits will be sought in patient neurons in vitro. Expression profiling results will guide our exploration of cellular phenotypes.

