**Fig. 2 Fig2:**
[figure not shown]
Using cellular phenotypes to identify likely lithium-responsive genes. To reduce the number of comparisons and preserve statistical power, iPSC-derived neurons will be used to identify a smaller number of genes likely to be involved in lithium’s action. iPSC-derived neurons from lithium responders and non-responders will be treated both with and without lithium. RNAseq will be conducted and genes sought whose expression changes in responders but not non-responders. These genes will comprise a limited number of a priori hypotheses for initial testing

The gene expression data will also be used to develop gene expression networks that can then be compared between the four conditions. It is likely that, more than specific genes, it is changes in the functional modules or groups of genes that are most robustly changed in response to lithium. Such a network-based approach may also be more informative regarding the biology that is altered by lithium and different in responders.

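### The iPSC candidate-gene rule compares two separate significance calls and does not test whether lithium's effect differs between responders and non-responders

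*Protocol article*

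**What the plan says.** The section on gene expression studies sets the rule: "Genes whose expression is significantly changed in response to lithium in responders but not non-responders will comprise a set of high-priority candidate genes". The Specific aims give it without a significance qualifier: "Genes whose expression is altered by lithium in lithium responders and not non-responders will be identified as possibly involved in lithium response". The Fig. 2 legend repeats it: "genes sought whose expression changes in responders but not non-responders".

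The sample is small: "Fibroblasts from 10 lithium responders and 10 non-responders will be reprogrammed". Cells from each line are studied with and without lithium.

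The gene expression section also states what the rule is meant to capture: "This strategy assumes that some of the same genes displaying differential change in expression also contain the variants affecting lithium response". The legend gives the use of the list: "These genes will comprise a limited number of a priori hypotheses for initial testing". The Power section makes SNPs from this work one of four sources for a stage 1 that is kept small to protect power. The other three are ConLiGen, the group's own retrospective sample and the literature.

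Nowhere does the article describe a gene-level test of the difference in lithium effect between the two groups. The comparison of expression networks across the four conditions, mentioned after Fig. 2, is a separate analysis and does not choose the genes.

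**The concern.** Significance in one group and non-significance in the other do not show that the groups differ. With 10 lines per group, a non-significant result in non-responders is weak evidence that lithium does nothing there. A gene with the same true lithium effect in both groups passes whenever chance puts it over the threshold among responders and under it among non-responders.

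The rule also errs the other way. A gene that changes clearly in both groups, but more in one or in opposite directions, is excluded because non-responders are significant too. Such genes show exactly the differential change the strategy is looking for.

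At stake is the quality of one screening list. Each equally responding gene on it brings SNP tests into stage 1 without the evidence of differential response that was meant to justify them.

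**Working it through.** **The plan's own figure.** The article gives no power, threshold or gene count for this selection step, so there is nothing to reproduce. Its one power statement (about 80% for a hazard ratio of 1.4 with 700 subjects) concerns the SNP survival analysis and does not bear on the rule.

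**Inputs from the article.** There are 10 lines per group, with and without lithium (Specific aims). For the pool of lithium-responsive genes, the section on lithium-mediated gene expression says of a human neuronal cell line: "they reported 347 upregulated and 324 downregulated genes", so 347 + 324 = 671.

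**Assumptions, not in the article.** A paired t-test in each group; effects d in SDs of the within-line change; per-gene alpha of 0.05 or 0.001; 15,000 genes tested.

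**Formulas.**
- Per-group power: p = P(|T| > t critical), with T noncentral t on 9 df and noncentrality d√10.
- Equal effect in both groups: the rule passes the gene with probability p(1−p), which is largest, 25%, at p = 0.5.
- Direct test: two-sample t on the within-line changes, 18 df, noncentrality (difference in d)·√(10/2). An equally responding gene passes with probability alpha, whatever its effect.

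**Chance that an equally responding gene passes the rule.**

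| d (SD) | p, alpha 0.05 | passes | p, alpha 0.001 | passes |
|---|---|---|---|---|
| 0.5 | 29% | 21% | 1.7% | 1.7% |
| 0.7 | 51% | 25% | 4.8% | 4.6% |
| 1.0 | 80% | 16% | 16% | 13% |
| 1.5 | 99% | 1.3% | 53% | 25% |
| 2.0 | >99.9% | <0.1% | 87% | 11% |

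The direct test passes 5% and 0.1% in every row. A simulation of 200,000 genes at alpha 0.05 gave 24.8% at 0.66 SD and 15.9% at 1.0 SD for the rule, against 5.0% for the direct test. Of the equally responding genes that passed the rule, only 9–10% had an interaction p-value below 0.05.

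**Total false candidates.** Suppose that 671 of 15,000 genes respond equally and the other 14,329 do not respond. A null gene passes the rule with probability alpha(1−alpha). Effects run from 0.5 to 1.5 SD.
- Alpha 0.05: nulls 14,329 × 0.05 × 0.95 = 681, plus 8 to 168 equal responders, gives about 689–848. The direct test gives 15,000 × 0.05 = 750.
- Alpha 0.001: nulls 14,329 × 0.001 × 0.999 = 14, plus 11 to 167, gives about 26–181. The direct test gives 15,000 × 0.001 = 15.

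At 0.05 the null genes dominate and the two methods are similar. At 0.001 the rule is clearly worse.

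**Share of equal responders in the list.** With 1–10% of the 15,000 genes responding equally, 1–5% responding only in responders, and effects of 0.8–1.5 SD, the share is about 0–33% at alpha 0.05 and 8–84% at 0.001. For the direct test it is at most 9% and 7%.

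**Genes wrongly dropped, alpha 0.05.**
- 2 SD in responders and 1 SD in non-responders: the rule selects 0.9998 × (1 − 0.803) = 20%; the direct test (difference 1 SD) selects 56%.
- +1 SD and −1 SD: the rule selects 0.803 × (1 − 0.803) = 16%; the direct test (difference 2 SD) selects 99%.

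**Where the rule does better.** For a gene that changes only in responders, the rule selects 76% and the direct test 56% at 1 SD and alpha 0.05. At 1.5 SD and alpha 0.001 the figures are 53% and 33%.

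**The case against.** The strongest defence is that this is a discovery screen with 10 lines per group, where sensitivity matters. For a gene that truly changes only in responders, the stated rule is more sensitive. That stands, and it is the real price of the fix.

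The reach is also limited. iPSC genes are one of four stage 1 sources, ConLiGen SNPs are tested first, and neither the Cox model nor the full GWAS depends on this rule. An equally responding gene is not worthless either: the Fig. 2 legend also speaks of genes involved in lithium's action generally, and such a gene could carry a relevant variant. These points stand and lower the weight of the issue.

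A condensed article may leave the RNA-seq model and thresholds to a fuller document. That excuses missing detail. It does not excuse a selection rule that is stated three times and does not measure its declared target.

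Three stronger readings are tempting but unsupported:
- **Stage 1 is filled with equally responding genes, or the list is largely a random draw of lithium-responsive genes.** The share runs from near 0 to 84% on inputs the article does not give. At alpha 0.05 it is a minority, and with 1.5 SD effects only 1.3% of equal responders pass. The 671 genes come from one cell line, not from iPSC-derived neurons.
- **The rule inflates type I error of the SNP tests.** It changes which SNPs are tested, not the validity of each test.
- **Taking the 20 donors from the prospective cohort biases those tests.** Selection is on expression change, not on SNP association with relapse, and nothing in the article shows a coupling between the two.

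**Conclusion.** The concern holds in a limited form. As written, the rule does not test the differential change the strategy relies on. It passes an equally responding gene with probability p(1−p), up to 25%, where a direct test would hold this at alpha, and it tends to lose genes that change clearly but unequally in both groups.

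The consequence is dilution of the iPSC part of stage 1. In total false candidates this is small at alpha 0.05 (about 689–848 against 750) and potentially large at alpha 0.001 (about 26–181 against 15). Those totals rest on an assumed 15,000 genes, 671 of them equal responders, effects of 0.5–1.5 SD and paired t-tests. The p(1−p) result needs only independent groups and equal power in each.

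This should be corrected because the rule misses its own target and the correction is cheap. It does not threaten the trial's main analysis.

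**What to change.** Select candidate genes on the lithium-by-responder-status interaction in a donor-paired RNA-seq model, with FDR control applied to that interaction. Use the within-group results only to describe direction and pattern. Align the wording in the Specific aims, the gene expression section and the Fig. 2 legend.

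The change is one contrast on the same data, with no new samples. Its cost is sensitivity to responder-only effects with 10 lines per group, as quantified above, and FDR control may leave a short list. If the investigators prefer a more sensitive screen, they can set a more lenient FDR level on the interaction in advance, so that the trade-off is explicit and the list still reflects a difference between groups.
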